
### Procedure

The flow of participants through the study is outlined in Fig. 5. Following baseline testing and imaging, eligible participants will be randomly allocated into one of three groups: (1) CSI, (2) exercise, education and load management programme, or (3) wait and see. Participants will complete the questionnaire outcome measures at baseline and 4, 8, 12, 26 and 52 weeks after commencement of the study, and physical outcome measures (abductor muscle strength and lag) will be reassessed at 8 weeks. Regular contact will be maintained with participants via phone calls and emails to ensure completion and return of questionnaires at all time points. Participants will be asked to refrain from seeking other treatments during the study period, but analgesia and anti-inflammatory drugs will be permitted. All medication use and co-interventions will be recorded.

**Fig. 5 Fig5:**
[figure not shown]
Flow of participants through RCT

### Not per protocol treatments

All participants will be informed of the importance of following allocated treatments, but encouraged to record in their diary any deviations from protocol. Not per protocol treatments are for example, medications, other injections, other physiotherapy or treatment not specified by the allocation.

### Adverse events

Participants, physiotherapists and medical practitioners performing the treatments will report adverse effects to the research assistant who with the chief investigator will then ensure that if required the appropriate treatment for that adverse effect is undertaken and that the event is reported to the ethics committee. The participant will be monitored over the course of resolution.

### Data management

The responses to the GROC scale will be dichotomized, where “Success” will be defined as “Moderately better” to “Very Much Better”. The proportion of improved participants from each group will determine success of the intervention.

### Sample size

The treatment effect will be evaluated by comparing success rates on the primary outcome measure of the GROC score between groups. For the global rating of change score, sample size is based on the ability to detect a clinically relevant difference of 30 % in success rate between the two treatment groups and the control at eight weeks from baseline using the Dunnett’s test procedure. This sample size accounted for a 15 % loss to follow-up, a type I error rate of 0.05, any-pair power of 0.95 and all-pair power of 0.80. Assuming a success rate of 40 % for the control (the wait and see group), 70 % for the physiotherapy group and 70 % for the CSI group, the target sample size was calculated at 67 patients per group for a total sample size of 201 which is based on 2000 Monte Carlo sampling with the equivalence margin of 20 %. This sample size was chosen because a sample size of 61 per group was required for a point estimate of effect of two points on the 11 point pain numerical rating scale (the other primary outcome). The Clinical Trial and Biostatics Unit of the Berghofer Queensland Institute of Medical Research was responsible for calculating sample size.

### Statistical analysis

Statistical analyses will be conducted on a blinded intention-to-treat basis, with all participants who were initially randomised into the study included where data are available for each measurement time point.

The outcomes measured at baseline, 4, 8, 12, 26 and 52 weeks will be analysed using linear mixed and logistic regression models that will include their respective outcome measure scores as a covariate, participants as a random effect and treatment conditions as fixed factors. Variables such as age, sex, body mass index (BMI) and site will be included as covariates in the analysis. Regression diagnostics will be used to check for normality of the measures and homogeneity of variance where appropriate. Treatment mean contrasts will be defined a-priori: CSI versus load modification and exercise intervention, CSI versus wait and see approach, and load modification and exercise intervention versus wait and see approach. Alpha will be set at 0.05. Numbers needed to treat index will also be calculated.

The cost and utility data will be analysed in a manner consistent with the clinical outcome data. The resource use data captured by the OCC-Q will be valued using unit costs derived from local and national sources. If the cost data violate the assumptions of parametric statistics, non-parametric methods of analysing group means will be used. Non-parametric bootstrapping will be used for calculating means and confidence intervals. Estimates of the costs and effects of each treatment group in relation to the comparator and to each other will be presented, with sampling uncertainty. The incremental differences between these groups will be reported as incremental cost-effectiveness ratios (ICER), reported from both the societal perspective (primary) and the health system perspective (secondary), and will be presented in cost-utility scatter planes. Confidence intervals will be calculated for the ICERs. Sensitivity analyses will also be conducted to test the robustness of the models. Cost-effectiveness acceptability curves (CEACs) will also be calculated to determine the likelihood that the treatments can be considered cost-effective at the commonly accepted, policy-relevant willingness-to-pay (WTP) thresholds of one, two, and three times GDP per capita.

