### Outcome measures

A battery of primary and secondary outcome measures will be recorded. They are summarized in Table 4.

**Table 4 Tab4:** Primary and Secondary Outcome measures

Primary outcomes	Measurement	Baseline	4 weeks	8 weeks	12 weeks	26 weeks	52 weeks
Average Pain over the last week	11-point Pain Numeric Rating Scale (NRS), with terminal descriptors of 0 = ‘no pain’ and 10 = ‘worst pain possible’	√	√	√	√	√	√
Perceived overall change in condition of Hip	Global Rating of Change Scale		√	√	√	√	√
Secondary Outcomes	Measurement						
Global Impact of pain	Lateral Hip Pain Questionnaire	√	√	√	√	√	√
Function	Patient Specific Functional Scale	√	√	√	√	√	√
Quality of life	EuroQoL	√	√	√	√	√	√
Muscle strength	Static painfree abductor muscle strength	√		√			
Muscle Function	Active Lag Abductor Muscles	√		√			
Pain Catastrophising	Pain Catastophising Scale	√	√	√	√	√	√
Depression	PHQ-9	√	√	√	√	√	√
Pain and Function	VISA-G	√	√	√	√	√	√
Pain Self-Efficacy	Pain Self-Efficacy Questionnaire	√	√	√	√	√	√
Physical Activity Levels	Active Australia Survey	√	√	√	√	√	√
Economic Costs	OCC-Q	√				√	√

*EuroQoL* European quality of life questionnaire, *PHQ-9* patient health questionnaire-9; *OCC-Q* osteoarthritis costs and consequences questionnaires

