#### Primary outcome measures

There are two primary outcome measures: (1) Global Rating of Change Score, and (2) Average Pain over the previous week.The Global Rating of Change Scale (GROC) is an 11-point scale in which the participant is asked to rate their perceived overall change in condition of their hip from the time that they began the study until the present, as Worse, No Change, or Better. If they indicate worse, the patient will then be asked *how much* worse on a five-point scale from Very Much Worse to Slightly Worse, and if they are better, they will be asked *how much* better on a five-point scale from Slightly Better to Very Much Better [31] (Fig. 3). Measuring patient perceived change using scales such as the GROC scale has previously been shown to be clinically relevant and a stable concept for interpreting meaningful improvements from an individual perspective [32].The average pain over the previous week is measured on an 11-point Pain Numeric Rating Scale (NRS), with terminal descriptors of 0 = ‘no pain’ and 10 = ‘worst pain possible’. The minimum important difference (MID) for the NRS has been found to be -1.5 points for musculoskeletal disorders [33].

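### The rule that adjusts each outcome for its own score has no baseline value to use for GROC, a primary outcome, and names no severity covariate in its place

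*Protocol article*

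**What the plan says.** The Statistical analysis section states the model in one sentence: "The outcomes measured at baseline, 4, 8, 12, 26 and 52 weeks will be analysed using linear mixed and logistic regression models", models "that will include their respective outcome measure scores as a covariate", with participants as a random effect and treatment as a fixed factor. It then adds: "Variables such as age, sex, body mass index (BMI) and site will be included as covariates in the analysis".

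Under Primary outcome measures, "There are two primary outcome measures: (1) Global Rating of Change Score, and (2) Average Pain over the previous week". The participant rates change in the hip "from the time that they began the study until the present". Table 4 lists this item as "Perceived overall change in condition of Hip" and ticks weeks 4, 8, 12, 26 and 52, with an empty baseline cell. The pain rating has all six ticks. Under Data management, "The responses to the GROC scale will be dichotomized", with success running from moderately better upwards, so GROC is the evident target of the logistic model.

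The Concealed allocation section says that envelopes are opened only after all baseline measurements are complete.

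**The concern.** A covariate rule stated for every outcome should work for the primary outcomes first. Here the covariate is not identified as a baseline value, and for one of the two primary outcomes no such value exists. The article gives no exception and no substitute.

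Two things are at stake. First, the GROC success model has no named measure of how severe the condition was at entry, although one is already on file for each participant. Second, the analyst must decide later whether to add one. In a logistic model that decision matters beyond precision, because adding a prognostic covariate also changes the conditional odds ratio being estimated. It is better settled in the text than after the data are seen.

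A lesser issue is that the sentence lists baseline among the analysed time points. If that is taken as a list of response rows, baseline becomes both response and covariate for every outcome that has a baseline score.

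**Working it through.** **1. The plan's own figure.** The Sample size section gives 67 per group for GROC success at 8 weeks (40 % against 70 % and 70 %, Dunnett's procedure, type I error 0.05, any-pair power 0.95, all-pair power 0.80, 15 % loss). After loss, 67 × 0.85 = 56.95, about 57 evaluable per group. A simulation of 200,000 trials, with a two-sided Dunnett critical value of 2.212 (two comparisons, correlation 0.5), gives:

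| Evaluable per group | Any-pair power | All-pair power | Inflated, n/(1 − 0.15) | Inflated, n × 1.15 |
|---|---|---|---|---|
| 57 | 0.949 | 0.782 | 68 | 66 |
| 58 | 0.954 | 0.798 | 69 | 67 |

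All four inflated values lie within 2 of 67, so the figure reproduces. No baseline covariate enters the calculation as described, so the covariate rule does not change it.

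**2. The rule applied to each primary outcome.**

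| Reading of the covariate | Pain rating (baseline ticked) | GROC (no baseline tick) |
|---|---|---|
| Baseline score of the same outcome | Ordinary baseline-adjusted model | No such score; the term is empty |
| The outcome's own score, literally | Circular | Circular |

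The empty cell for GROC is not an accident of table layout, since a rating of change since entry has no value at entry. Under the sensible reading, the named covariates left for GROC are age, sex, BMI and site.

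**3. Baseline as a response row (outcomes with a baseline score only).** Suppose baseline is kept as a response, the model has a treatment main effect and no treatment-by-time term, data are complete, and the true effect is a constant d at the five later visits. The effect at baseline is zero, so the main effect averages to (0 + 5d)/6 = 5d/6. With an assumed d of −1.5 pain points this is −1.5 × 5/6 = −1.25. A simulation on assumed values (two arms of 57, between-person SD 1.4, residual SD 1.4, 3,000 runs) gives −1.25 with baseline as a response row and −1.50 without it. Contrasts at a single visit from a treatment-by-time model would not be diluted in this way.

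**The case against.** The strongest reply is that this is a wording slip in a condensed article. Most of that reply stands.

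- A reader might infer that each outcome is adjusted for its own concurrent score, which would remove the treatment effect. That is not a plausible plan; the word baseline was almost certainly dropped.
- A reader might infer that the GROC model cannot be fitted. The document does not support this. Without the term, treatment, the participant effect and the four named covariates remain. The covariate list is also open-ended, so baseline pain is not excluded.
- A reader might infer that the plan shrinks its treatment effects by a sixth. The list of weeks can be read simply as the visit schedule. It cannot be a literal list of responses for every outcome, because Table 4 measures strength and abductor lag only at baseline and week 8, and costs only at baseline, 26 and 52 weeks. The article states no time terms, and the two primary hypotheses concern week 8 and week 52. The shrinkage cannot occur for GROC at all, since GROC has no baseline row.
- The article gives no association between baseline pain and GROC success, so the precision forgone cannot be stated.

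The mismatch over GROC survives. The article does not merely leave a detail to a later plan. It states a rule for all outcomes that its own schedule and its own definition of a primary outcome do not allow.

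**Conclusion.** The point holds in a limited form. As written, the covariate rule is empty for GROC under the sensible reading and circular under the literal one, and the article names no severity covariate in its place. The conclusion rests only on Table 4, the definition of GROC and the wording of the model sentence.

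Its size is modest. The sample size of 67 per group is unaffected, and the GROC analysis remains feasible and unconfounded by design, because allocation is randomised. What is lost is an unquantified amount of precision and the advance choice of the adjusted estimand for a primary outcome.

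The 5/6 dilution is conditional. It applies only to outcomes with a baseline score, and only if baseline is retained as a response row in a model with a treatment main effect alone. The document does not establish that this is the intended model.

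**What to change.** Replace the covariate clause in the Statistical analysis section with text such as:

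*Responses are the post-baseline visits at which each outcome is scheduled in Table 4. Each model includes the baseline value of that outcome as a covariate where one is measured. The GROC success model includes baseline average pain (NRS) instead.*

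Tying the responses to Table 4, rather than to one fixed list of weeks, keeps the sentence correct for strength, abductor lag and the cost questionnaire. The change costs one sentence. It needs no new data, because baseline pain is already recorded on every participant before allocation, and it leaves the sample size as it is. If a separate analysis plan already says this, the article's wording need only be aligned with it.

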Most patients and their medical practitioners understandably seek a positive early response. Although Rompe et al report patient satisfaction with a slow rate of improvement in the early stages, a 7 % success rate for home exercise after 1 month [13] is not convincing evidence to recommend exercise to a patient who would otherwise have a 75 % chance of a successful early outcome with CSI. In contrast, outcomes from exercise and manual therapy for a comparable tendinopathy at the elbow (tennis elbow or lateral elbow tendinopathy, with similar age demographic) are comparable to those from CSI at 6 weeks (65 and 78 % success rates respectively) and superior to adopting a wait and see approach [21]. We speculate that the low success rates at 1 month reported by Rompe et al., in contrast to the high early success rates reported by Bissett et al., is the non-specific nature of the prescribed exercises (i.e. not targeting the muscles specifically affected by tendinopathy, using stretches that increase compression), a lack of specific load modification and management strategies related to tendon healing, and a low level of supervision of the home-based exercise programme.

The contemporary non-operative approach to effectively managing tendinopathy involves specific exercise for the affected muscles and load management in the form of advice and practical strategies [15]. This approach has yet to be rigorously tested in an RCT. We propose to test different conservative management options for gluteal tendinopathy by comparing an exercise and load management approach supervised by physiotherapists, CSI and the adoption of a wait and see approach.

Our primary hypotheses are that:HI: Both the exercise and load management programme and the CSI will be superior to a wait and see approach in terms of treatment success rates based on global rating of change and reductions in pain at 8 weeks.H2: The exercise and load management programme will be superior to CSI in terms of treatment success rates and reductions in pain at 52 weeks.

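### The sample size rests on Dunnett's adjustment for two comparisons with control, but the analysis section names three contrasts at 0.05 and does not carry the adjustment over

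*Protocol article*

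**What the plan says.** - **Sample size** (protocol article). The calculation concerns GROC success "between the two treatment groups and the control at eight weeks from baseline using the Dunnett’s test procedure", with "a type I error rate of 0.05, any-pair power of 0.95 and all-pair power of 0.80". The rates are 40% for wait and see and 70% for each active group, loss to follow-up is 15%, and the result is 67 per group (201 in total). The section adds that 61 per group were needed for a two-point pain effect, and gives no SD, power or alpha for that figure.
- **Statistical analysis.** Three contrasts are fixed in advance: CSI versus exercise, CSI versus wait and see, and exercise versus wait and see. The only statement on error rate is "Alpha will be set at 0.05".
- **Primary outcome measures.** "There are two primary outcome measures": GROC and average pain over the past week.
- **Background, hypotheses.** H1 says both active treatments beat wait and see at week 8 on success rate and on pain. H2 says exercise is "superior to CSI in terms of treatment success rates and reductions in pain at 52 weeks".

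The article states no testing order, no split of alpha, and no rule on whether one or both outcomes must succeed.

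**The concern.** The two sections describe different families of tests. In the sample size, 0.05 is a family-wise rate over two comparisons with control on one outcome at one visit. In the analysis, 0.05 is attached to three contrasts, one of which (CSI versus exercise) lies outside the family that Dunnett's many-to-one procedure protects. That contrast is the whole of H2. Pain, the second primary outcome, also lies outside it.

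An analyst following the analysis section literally would test each contrast at 0.05. The error rate that justified 201 participants would then not be the error rate of the reported analysis. This is a mismatch between two stated parts of the plan, and not only a detail left for later.

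**Working it through.** **Inputs.** From the sample size section: success rates 0.40, 0.70 and 0.70, type I error 0.05, loss 15%, 67 per group, "any-pair power of 0.95 and all-pair power of 0.80". The contrasts come from the analysis section and the hypotheses from the background. Sidedness is not stated. The correlations between outcomes and between visits are not in the article and are assumed.

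**1. Reproduce 67 per group.** With equal arms, two comparisons that share a control have test statistics correlated 0.5. The two-sided Dunnett critical value c solves P(|Z1| ≤ c and |Z2| ≤ c) = 0.95. This gives c = 2.212, or a per-comparison level of 0.0270. Evaluable patients are 67 × 0.85 = 56.95, about 57; alternatively 58 × 1.15 = 66.7, rounded to 67. Power was simulated with pooled two-proportion z tests:

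| Evaluable per group | Critical value | Any-pair power | All-pair power |
|---|---|---|---|
| 57 | 2.212 (Dunnett) | 0.948 | 0.78 |
| 58 | 2.212 (Dunnett) | 0.954 | 0.80 |
| 50 | 1.96 (unadjusted) | 0.954 | 0.80 |
| 57 | 1.96 (unadjusted) | 0.968 | 0.84 |
| 58 | 1.96 (unadjusted) | 0.971 | 0.85 |

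The stated powers of 0.95 and 0.80 at 67 per group are recovered with two-sided Dunnett. Unadjusted tests, or one-sided Dunnett, would reach them with about 50 evaluable (50/0.85 = 58.8, so 59 randomised). The 0.05 in the sample size is therefore a family-wise rate.

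**2. Error rate if each contrast is tested at two-sided 0.05.** Under the global null, the arm means are independent normal variables and each contrast is a scaled difference of two of them. The family-wise rate is P(at least one |Z| > 1.96).

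| Family | Tests | Chance of ≥ 1 false positive |
|---|---|---|
| Two active-versus-control contrasts, GROC, week 8 | 2 | 9.1% (Dunnett: 5.0%) |
| Three contrasts, one outcome, one visit | 3 | 12.2% |
| GROC tests of H1 (week 8) and H2 (week 52) | 3 | about 13% |
| H1 on both outcomes, any one counts | 4 | 13–17% |
| H1 and H2 on both outcomes, any one counts | 6 | 18–25% |

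The first two rows need no assumed correlation. The third depends little on the between-visit correlation: 13.1–13.7% for values from 0 to 0.6. The last two take the between-outcome correlation from 0 to 0.9 and, for six tests, the between-visit correlation from 0.3 to 0.6.

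**3. Dunnett alone does not close the gap.** Applying c = 2.212 to all three contrasts on one outcome at one visit still gives about 6.9%, because the third contrast is outside the procedure.

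**4. Joint reading.** If H1 needs all four of its tests and H2 needs both of its tests, each is an intersection-union test and is held at 0.05 or less without adjustment. If both hypotheses sat at that limit and were independent, the chance of at least one false claim would be 1 − 0.95² = 0.0975.

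**The case against.** - **The analysis section does not say unadjusted.** True. Its 0.05 could be meant family-wise, as in the sample size, and an analysis plan that is not shown may give the procedure. Silence alone would not be a finding. What stands is that the one procedure the article names cannot cover the contrasts and outcomes that the article makes primary.
- **H1 and H2 are worded as joint claims.** H1 says both treatments, and each hypothesis joins success and pain with an and. The all-pair power of 0.80 fits that reading, and on it each hypothesis needs no adjustment. But the any-pair power target counts a single significant comparison, and an all-or-nothing H1 would not have needed Dunnett. The text supports neither reading firmly.
- **A reader might infer a false-positive risk of 18–25%.** That needs a rule under which any one of six tests is a win, which appears nowhere. The data management section says the proportion improved will determine success, and the sample size section evaluates the effect on GROC. Both point to GROC as the decision outcome, and so to about 13%. The rates also count errors in either direction, while the hypotheses are directional; false superiority over control on the two week-8 GROC contrasts is about 4.6%.
- **A reader might infer that about 8 participants per group (67 − 59) were recruited for an adjustment that is not applied.** The article does not support this: pain required 61 per group, above 59. At most 67 − 61 = 6 are at issue, and none if the 61 means evaluable patients (61/0.85 = 71.8, so 72).

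**Conclusion.** The concern holds as a mismatch between the sample size and analysis sections. The 67 per group is not wrong, and it reproduces with two-sided Dunnett. The analysis section does not carry that adjustment forward, and adds a contrast and an outcome that it does not cover.

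Followed literally, the two-sided error rate under the global null is 9.1% rather than 5% for the comparisons the trial was sized on, and about 13% once the week-52 GROC contrast is added. Both figures assume that each contrast is tested at 0.05, which is inferred from the absence of any stated adjustment. Larger figures depend on an any-one-wins rule and on assumed correlations. The joint reading removes the inflation within each hypothesis. Because the article does not choose between these readings, its true error rate cannot be determined from the text.

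**What to change.** In the statistical analysis section:

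1. Report Dunnett-adjusted p-values and confidence intervals for the two active-versus-wait-and-see contrasts at week 8, as the sample size assumes.
2. Name exercise versus CSI at week 52 as the single contrast for H2.
3. State whether each hypothesis requires both GROC success and pain, or either one. If either suffices, add an adjustment across the two outcomes.
4. Label all other contrasts and visits as secondary.

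Testing H2 only after H1 is met, or using Holm across the two hypotheses, is optional. Gating would block the week-52 claim if H1 failed, and whether to adjust across two questions at different visits is debatable.

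**Cost.** No change to recruitment or data collection. The week-8 intervals widen slightly, by 2.212/1.96 = 1.13 in multiplier. GROC all-pair power is about 0.78–0.80 with Dunnett, against 0.84–0.85 unadjusted, at 57–58 evaluable per group, so the sample size already allows for it. Requiring both outcomes would lower the power of each claim further. That loss is not quantified here, because the article gives no SD for pain.
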